### 2. Secondary endpoints:

#### ○ Pharmacokinetics:

- The plasma peak detemir and glargine levels and the time from the respective peak levels to half maximum levels at the two dosages of both insulins
- The mean duration of insulin as defined by appropriately elevated detemir and glargine levels at each of the two dosages.
- The dose-equivalence of both, insulin glargine and detemir in terms of their glucose-lowering effect in obese patients with type 2 diabetes mellitus.

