### 3.3.2. Inpatient metabolic studies

Patients eligible to participate in the study based on the results of the screening visit will be admitted to the Department of Medicine, University Hospital Basel ([name]) at 7 am after fasting overnight for approximately 40 h, including an overnight stay. In patients on sulfonylureas these will be discontinued for 4 weeks before beginning the study and be withheld during the total duration of the study. Metformin will be paused 48 h (kinetic wash-out) and long-acting basal insulins will be paused 48-72 h prior to the study. If necessary, short-acting insulin will be given up to the evening prior to the study to keep blood glucose levels below 10 mmol/l.

An intravenous cannula will be inserted into an antecubital vein for the infusion of insulin and glucose. A second intravenous canula will be placed in a dorsal hand vein to obtain frequent blood samples for measurement of plasma glucose concentration.

At the beginning of the study a variable intravenous infusion of human soluble insulin will be started at 8 am to reach euglycemia at a plasma glucose level of 5.5 mmol/l within 30-60 minutes. At 10 am a single subcutaneous injection of either insulin detemir or insulin glargine will be administered in the thigh in two different dosages (0.8 and 1.6 IU/kg body weight) in randomized order. Intravenous regular insulin will be tapered when plasma glucose falls below 5.5 mmol/l.

Plasma glucose will be monitored at frequent intervals every 10 to 30 min (goal: plasma glucose 5.5 mmol/l; total blood needed 2 ml/measurement), and glucose 10% will be

administered by continuous i.v. infusion (syringe pump) using an algorithm to maintain plasma glucose levels at 5.5 mmol/l. Blood will also be drawn every 2 h for the first 6 h and subsequently every 6 h for the measurements of the serum concentrations of C-peptide, insulin detemir and insulin glargine using specific radioimmunoassays.

Each subject will be studied at four occasions in order to study the effects of two different doses (0.8 and 1.6 IU/kg body weight) of insulin detemir and of insulin glargine,, respectively. The procedures will be identical during each study. The time period between the different studieis always at least 7 days.

Each inpatient metabolic study will last 36 hours after the injection of insulin detemir or until the plasma glucose will consistently increase to > 8.3 mmol/l in the absence of glucose infusion.

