Subjects will not be permitted to eat during the inpatient study, but will be given a dinner meal after the end of the study before leaving the hospital. Noncaloric drinks will be given ad libitum throughout the study procedure. Patients will be blinded regarding the dose and type of insulin.

For each patient, the entire study will be finished after the fourth inpatient study has been completed.

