#### 3.5.3. Measurements and calculations

Performance of an euglycemic hyperinsulinemic clamp by hourly measurement of plasma glucose, insulin and C-peptide and calculation of the area under the curve (AUC) of the necessary glucose infusion rate (GIR) which is necessary to maintain plasma glucose at 5 mmol/l. For serum insulin and serum C-peptide, descriptive statistics for pharmacokinetic measures are performed (maximal serum insulin concentration [Cmax], time to Cmax [tmax], and AUC; minimal serum C-peptide concentration [Cmin], time to Cmin [tmin] and AUC).

End of insulin action is defined as the time at which plasma glucose consistently increases to > 8.3 mmol/l despite adaptation of glucose infusion.

Since it is debated, that a given unit of insulin detemir is equipotent to a given unit of insulin glargine, we compare the activity ratio (standardized activity ratio) of the two insulins by the total glucose consumption (g glucose/U of insulin administered). This activity ratio will be used to determine further pharmacodynamic effects like the peak of action, the time from peak to half maximal action and the total duration of action.

We will perform a mixed model with a random subject effect in order to calculate differences between the two different dosages and the different insulins (total glucose consumption, duration of action). Among others, covariates that will be assessed include BMI, age, sex.

As there are several primary endpoints, a Bonferroni correction will be applied.

The sample size is small, but was determined by specifying a 95% CI with a relative width of 30% for the duration of action (12). However, as previous studies have used lower total insulin dosages and studied patients for maximal 24 hours, a very meaningful sample size calculation cannot be performed.

1ml of additional serum and plasma will be stored for batch analysis of cytokines and not yet defined parameters (not part of this protocol)

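### Hormone sampling appears to stop when the pharmacodynamic end of action is reached, so time to half-peak, duration of elevated levels and hormone AUC are observed over an outcome-dependent window

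*Protocol*

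**What the plan says.** Section 3.3.2 of the protocol sets the maximum session length: "Each inpatient metabolic study will last 36 hours after the injection of insulin detemir". It then allows an earlier ending that depends on glucose: "or until the plasma glucose will consistently increase to > 8.3 mmol/l in the absence of glucose infusion". For C-peptide, detemir and glargine levels it gives this schedule: "Blood will also be drawn every 2 h for the first 6 h and subsequently every 6 h". When the session is over, subjects "will be given a dinner meal after the end of the study before leaving the hospital". No hormone draw is described after that, and none is tied to the moment the session ends.

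Section 3.5.3 uses the same threshold for the pharmacodynamic endpoint: "End of insulin action is defined as the time at which plasma glucose consistently increases to > 8.3 mmol/l despite adaptation of glucose infusion". The primary endpoint in section 2 also ends the duration of action at 8.3 mmol/l or at 36 h.

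The secondary kinetic endpoints in section 2 include "the time from the respective peak levels to half maximum levels at the two dosages of both insulins" and "The mean duration of insulin as defined by appropriately elevated detemir and glargine levels at each of the two dosages". Section 3.5.2 states a null hypothesis of no difference in peak level and time to half-peak. For Cmax, tmax and AUC, section 3.5.3 says only that "descriptive statistics for pharmacokinetic measures are performed", with no time window for the AUC.

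Sections 1 and 6 both say that insulin action lasts longer at higher doses. Section 1 cites durations of 12 to 23 h for detemir and 22 ± 4 h for glargine, in type 1 diabetes.

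**The concern.** Time from peak to half-maximum, duration of elevated levels and AUC all depend on the tail of the concentration curve. If sampling ends when the glucose-lowering effect ends, the part of the tail that is seen depends on the pharmacodynamic result of that session. The window then differs between doses, between insulins and between patients, and it should tend to be shorter at the lower dose and for the shorter-acting insulin.

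Two things are at stake. First, part of any difference between doses or insulins in these measures would reflect length of observation, not kinetics. Second, kinetics and dynamics would look more concordant than they are, because a short effect also shortens the record of the hormone. A later analysis plan can choose a common window or a censoring rule, but it cannot recover a sample that was never drawn.

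**Working it through.** The plan gives no figure for this point, so there is none to reproduce. The sample-size statement in section 3.5.3 concerns duration of action only.

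**Step 1: what each session yields.** On the section 3.3.2 schedule the post-dose draws fall at 2, 4, 6, 12, 18, 24, 30 and 36 h, eight in a full session.

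| Session ends at | Draws obtained | Last draw |
|---|---|---|
| 12 or 16 h | 4 of 8 | 12 h |
| 20, 22 or 23 h | 5 of 8 | 18 h |
| 26 h | 6 of 8 | 24 h |
| 30 h | 7 of 8 | 30 h |
| 36 h | 8 of 8 | 36 h |

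A session ending just before a scheduled draw leaves a last level almost 6 h old; for example, an end at 17 h leaves a last level at 12 h (17 − 12 = 5 h). This is conditional: section 3.5.3 describes hourly measurement of insulin and C-peptide. If that covers the two analogues, the gap is at most about 1 h.

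**Step 2: effect on AUC, as an illustration.** Assumptions, not protocol figures: dose-proportional one-compartment kinetics, absorption half-life 3 to 6 h, apparent half-life 8 to 18 h. Doses 0.8 and 1.6 IU/kg are from section 3.3.2. With ka and ke equal to ln 2 divided by the respective half-life, and volume and bioavailability cancelling:

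A(T) = ka/(ka − ke) × [(1 − e^(−ke·T))/ke − (1 − e^(−ka·T))/ka]

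Ratio to session end = (1.6/0.8) × A(T at high dose) / A(T at low dose)

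- Half-lives 3 h and 8 h: A(20) = 8.345, A(28) = 9.920, A(30) = 10.176, A(36) = 10.727.
- Half-lives 6 h and 18 h: A(20) = 9.224, A(28) = 13.228, A(30) = 14.105, A(36) = 16.433.

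| End, low vs high dose | Half-lives 3 h, 8 h | Half-lives 6 h, 18 h |
|---|---|---|
| 36 vs 36 h | 2.00 | 2.00 |
| 30 vs 36 h | 2 × 10.727/10.176 = 2.11 | 2 × 16.433/14.105 = 2.33 |
| 20 vs 28 h | 2 × 9.920/8.345 = 2.38 | 2 × 13.228/9.224 = 2.87 |
| 20 vs 36 h | 2 × 10.727/8.345 = 2.57 | 2 × 16.433/9.224 = 3.56 |

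The true ratio is 2.0, and over any common window the formula returns 2.0.

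**Step 3: is the loss uneven, and is half-peak reached?** A second illustration used a fast half-life of 2 h and slow half-lives of 6, 8 or 12 h. The low-dose stop was set at 14, 18, 22 or 26 h. The high dose stopped at the same concentration, capped at 36 h. That makes 3 × 4 = 12 scenarios.

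- AUC from 0 to 36 h lost by stopping early: 5% to 45% at the low dose and 0% to 14% at the high dose; the low dose lost more in all 12.
- Half-peak fell after the last low-dose draw in 5 of 12 scenarios, and after the last high-dose draw in none. Example: slow half-life 12 h and low-dose stop at 22 h, with half-peak at 21.3 h and last draw at 18 h.

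**The case against.** The strongest reply is that the documents support less than a reader might infer from this mechanism. Most of that reply stands.

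- **That a planned AUC ratio is biased.** Hormone AUC is not among the secondary endpoints in section 2, has no hypothesis in section 3.5.2 and is only descriptive in section 3.5.3. No between-dose AUC ratio is planned, and AUC to session end is not stated as the window. The ratios above show what a naive comparison would give.
- **That kinetic duration can never exceed pharmacodynamic duration.** This does not follow. Section 2 starts duration of action at the 50% reduction in intravenous insulin and fixes no start for the kinetic duration, so the kinetic duration could be the longer. Only the end of observation is shared.
- **That any crossing of 8.3 mmol/l ends a session.** The rule requires a consistent rise without glucose infusion.
- **That time to half-peak is lost in every short session.** It is lost only where half-peak has not been sampled by the end. In the model of step 2, half-peak falls between 19.5 h and about 42 h; values beyond 36 h are lost to the 36 h limit even in a full session.
- **That early endings will be common.** The cited durations come from type 1 diabetes. Fasting, severely obese patients with type 2 diabetes may often reach 36 h.

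It is also fair to say that no sentence states outright that hormone draws stop with the session, and that an AUC window and censoring rules could sit in a statistical analysis plan that is not shown. On the first, the inference from a meal and discharge is clear. On the second, the absence of a closing sample is a matter of protocol procedure that no later plan can repair.

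**Conclusion.** The point holds in limited form. As written, the two secondary kinetic time endpoints and the descriptive hormone AUC are observed only until the session ends, and the session may end on the pharmacodynamic outcome. Comparing them between doses or insulins without allowing for this would be biased, probably with more lost at the lower dose. That direction rests on the protocol's own premise of dose-dependent duration.

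The size cannot be fixed from the document, because the share of sessions ending early is unknown. Under the assumed kinetics, a true AUC ratio of 2.0 would appear as anything from 2.0 (all sessions complete) to about 3.6 (20 versus 36 h). Cmax and tmax are little affected if the peak comes early, and the primary pharmacodynamic endpoints are untouched. The point deserves action because the repair is cheap, but it does not threaten the main conclusions of the trial.

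**What to change.** - **Section 3.3.2:** add one sample for C-peptide and the study insulin at the moment each session ends, whatever the reason for ending. The rule that ends the session is unchanged.
- **Sections 3.3.2 and 3.5.3:** reconcile the 2-hourly then 6-hourly draws with the hourly insulin and C-peptide measurement.
- **Section 3.5.3:** treat time from peak to half-maximum and duration of elevated levels as right-censored at the closing sample when the level has not fallen far enough. Since a session ends as the effect wanes, this censoring may be informative. Report the number of censored sessions by dose and insulin, and do not average only the observed times.
- **Section 3.5.3:** make any comparison of hormone AUC between doses or insulins over a common within-patient window, from injection to the end of the shortest of the patient's four sessions. AUC to session end can stay as description.

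The cost is at most one small draw per session: four per patient, 12 × 4 = 48 in all, and none where the 36 h draw already closes the session. Late data from the longer sessions go unused in the AUC comparison only.

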### 1. Primary endpoint:

#### ○ Pharmacodynamics:

- The glucose consumption over time to maintain euglycemia: i.e. the peak of action, the time from peak to half maximal action, the total duration of action will be assessed following a single subcutaneous injection of two different doses of insulin detemir and glargine.
- The total duration of action is defined as the time between the beginning of action (from the time of 50% reduction in intravenous insulin infusion) until the end of action when plasma glucose consistently exceeds 8.3 mmol/l after the glucose infusion had been stopped, or after 36 h, whichever comes first (12, 13) of both doses and of both insulins.
- If the glucose-insulin-lowering effects of the 2 insulins are not equal at identical insulin dosages, the pharmacodynamics will be compared at the same effect level (standardized activity ratio, see below).

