## **6. Significance and outlook**

With the increasing incidence and prevalence of type 2 diabetes mellitus, insulin therapy will be of major importance, because insulin is highly effective. Long-acting insulins like insulin detemir and insulin glargine are being used more and more frequently. Safety data about high doses of insulin are necessary and reassuring for physicians treating obese patients with insulin. As all insulins show a dose-dependent prolongation of their action profile, an examination of the effect of high doses, as often needed in insulin resistant states, is important for the prevention of hyper- and hypoglycaemia and thus for the safety and efficacy of insulin therapy.

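### Only patients are blinded; no masking is provided for clamp staff or for whoever times onset and end of action, so duration of action is open to observer bias

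*Protocol*

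**What the plan says.** Protocol section 3.3.2 states: "Patients will be blinded regarding the dose and type of insulin". No other section mentions blinding. Section 3.1 names two branded products from two sources and describes no masking or recoding. Section 3.4.2 gives the investigators oversight of both conduct and data handling.

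The endpoint is built as follows.

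- **Start of action** (section 2, primary endpoint): "from the time of 50% reduction in intravenous insulin infusion".
- **Taper of intravenous insulin** (section 3.3.2): "Intravenous regular insulin will be tapered when plasma glucose falls below 5.5 mmol/l".
- **End of action** (section 2): "until the end of action when plasma glucose consistently exceeds 8.3 mmol/l after the glucose infusion had been stopped", or 36 h if that comes first.
- **End of action** (section 3.5.3): "plasma glucose consistently increases to > 8.3 mmol/l despite adaptation of glucose infusion".
- **Sampling** (section 3.3.2): "Plasma glucose will be monitored at frequent intervals every 10 to 30 min".
- **Glucose infusion** (section 3.3.2): given "using an algorithm to maintain plasma glucose levels at 5.5 mmol/l".

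Section 3.5.1 names total glucose consumption and duration of action as the variables of the primary null hypothesis. Section 6 gives the expected result: "As all insulins show a dose-dependent prolongation of their action profile". Section 1 also describes dose-dependent duration.

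**The concern.** The patient reports nothing that enters the primary variables, so blinding the patient does little to protect them. Duration of action depends on what staff do with the intravenous insulin and on when somebody judges that glucose has stayed above the threshold. If those people know which insulin and dose were given, and the protocol itself tells them that a higher dose lasts longer, that expectation can influence both times.

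What matters for the comparison is differential handling. A habit applied equally in all four sessions largely cancels in the within-patient contrast. A habit that varies with dose or insulin does not cancel, does not average out over 12 patients, and cannot be separated from the treatment effect by the mixed model in section 3.5.3.

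**Working it through.** The protocol gives no figure to reproduce here. The check sets the endpoint definitions against the safeguards and then puts a scale on the discretion that is left.

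**1. Where judgement enters**

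- *Onset.* The event that starts the clock is a staff action. Section 3.3.2 gives a trigger for the taper (glucose below 5.5 mmol/l) but no step or rate, and section 2 does not say against which infusion rate the 50% is read. Section 3.4.1 adds that the infusion is lowered once the injected insulin begins to act. The perceived onset thus guides the taper, and the taper defines the onset.
- *End.* The threshold of 8.3 mmol/l is numeric, but *consistently* has no number or duration of readings. Section 2 and the session-end sentence in section 3.3.2 require that no glucose is running. Section 3.5.3 refers only to adaptation of the infusion, which could be read as allowing some glucose still to run. The same record could therefore give two end times.
- *Sampling.* The interval may be anything from 10 to 30 min, with no rule for choosing it.
- *Total glucose consumption.* The glucose infusion follows an algorithm (itself not specified) that works on measured glucose. Discretion is smaller here.
- *Cap.* A session that runs to 36 h needs no end-of-action call, so only the onset is left to judgement.

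**2. Scale of the discretion**

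Inputs: sampling interval 10 to 30 min (section 3.3.2); mean duration 22 h for glargine and a lower figure of 12 h for detemir (section 1). Both durations come from type 1 diabetes; using them for these patients is an assumption.

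Relative shift = shift in minutes / (duration in hours x 60).

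| Shift | Duration | Calculation | Result |
|---|---|---|---|
| One interval, 10 min | 22 h | 10 / 1320 | 0.8% |
| One interval, 30 min | 22 h | 30 / 1320 | 2.3% |
| 30 min at each end | 22 h | 60 / 1320 | 4.5% |
| 30 min at each end | 12 h | 60 / 720 | 8.3% |

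**3. Comparison with planned precision**

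Section 3.5.3 plans a 95% confidence interval with a relative width of 30% for duration. Read as full width, this is ±15%, or 0.15 x 22 = 3.3 h. Read as half-width, it is ±30%, or 0.30 x 22 = 6.6 h. The shifts in the table are smaller than either. The comparison is for scale only: the interval describes random error, while a shift tied to dose would be systematic.

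**The case against.** The case against has real force on several points.

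- **Staff knowledge of the allocation is an inference.** A reader might conclude that the operators know the insulin and dose. The protocol does not say so, nor who prepares or gives the injection. It supports only that masking of these staff is not provided for.
- **A large bias is not shown.** A reader might add two extra readings at 30 min (1 h) to a taper begun 30 to 60 min early and reach 1.5 to 2 h, or 6.8 to 9.1% of 22 h. That sum takes the longest interval (at 10 min, two readings add 20 min), has no source for the early taper, and assumes that both errors point the same way.
- **A late call is not lost.** A reader might infer that the end-of-action call cannot be checked afterwards. If the operator waits too long, the earlier readings remain in the record and can be re-scored. Only a session ended too early loses data.
- **Safeguards exist.** The algorithm, the numeric threshold, the 36 h cap and the statement that procedures are the same in all four sessions limit discretion.
- **A single numeric definition would remove much of the end-of-action problem without masking.** This is right. It would not protect onset, because a log shows when the infusion was halved but not whether expectation prompted it.

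What stands is that the protocol settles who is blinded, leaves out those whose actions set the two times, and defines one of those times loosely and inconsistently. Masking is not out of reach in principle: the title of the detemir dose-response study cited as reference 12, on which section 2 relies for the duration definition, describes that study as double-blind.

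**Conclusion.** The point holds for duration of action. The protocol blinds patients only, bases onset on a staff action and end on an unquantified judgement with differing wordings, and states the expected direction of the dose effect. Total glucose consumption is less exposed and should not be put on the same footing.

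This is exposure to bias, not evidence that bias occurred. Its size and direction cannot be derived from the document. The 0.8 to 8.3% in the working shows what small timing shifts would mean, on durations borrowed from type 1 diabetes; *consistently* sets no upper limit. It should be corrected, but it does not invalidate the design.

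**What to change.** 1. **Section 3.3.2:** state who is blinded. Where feasible, keep insulin and dose from the existing staff who run the infusions, with a code that can be opened for safety. If masking is not feasible, say so and give the reason.
2. **Sections 2, 3.3.2 and 3.5.3:** reconcile the wordings into one operational definition of end of action for scoring, fixed in advance, that quantifies *consistently* and states the condition on the glucose infusion. Keep the 36 h cap. State the infusion rate against which the 50% reduction is read.
3. **Section 3.5.3:** have onset and end derived from coded glucose and infusion logs, with the times locked before unmasking. Flag any session that ended before the scoring definition could be applied.

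Step 1 is what protects onset. Steps 2 and 3 protect the end of action and are worth making even if operators cannot be masked.

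The cost is some reallocation of existing roles and the coding of logs. No extra patients or patient procedures are needed. Operators may still guess the dose from the glucose response, so masking may be incomplete. No rule for stopping a session, tapering insulin or any other clinical step is proposed here.
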